### Statistical methods

#### Statistical methods for primary and secondary outcomes.

Analyses will be performed on the ITT population for the primary and secondary endpoints, i.e., analyzing all randomized participants according to the arm they were randomized to. The analysis method will be ANCOVA of change from baseline with treatment as factor and baseline value as covariate at the corresponding post-baseline visit, i.e., month 12. Treatment difference point estimates will be reported together with 95% CIs and p-value. Missing values will be multiply imputed

For the exploratory endpoints, a modified ITT set will be used, requiring at least one post-baseline measurement for the inclusion in the analysis for each endpoint. The analysis method will be linear mixed effects model. Results will be reported for both post-baseline visits.

Details of model specifications, imputation methods & assumptions, sensitivity analyses and subgroup analyses will be provided in the statistical analysis plan (SAP), that will be made publicly available prior to data lock (i.e., before the dataset is finalized and analysis starts).

Results will be reported with a 95% confidence interval and p-value, using a 5% significance level.

Baseline demographic and clinical characteristics will be summarized for each group, using descriptive statistics (e.g., means, standard deviations, medians, and range for continuous variables, frequencies and proportions for categorical) to assess comparability between groups at baseline. Efficacy analysis will be conducted by a blinded and independent statistician with no contact to the participants in the trial. Reporting will follow CONSORT guidelines [63].

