### Trial design

The Dialogue study is a randomized parallel-group superiority clinical trial allocating a total of 96 patients to either VR-based avatar intervention plus treatment as usual (TAU) or TAU (see Table 1 for participant eligibility criteria) Participants will be randomly assigned to the intervention plus treatment as usual and TAU in a 1:1 ratio (48 participants in each group). As recruitment will take place from different treatment sites, TAU may consist of various forms of treatment courses, all provided by health professionals. These treatments may include individual or group psychotherapy, and for some participants, complementary dietary guidance and/or meal support, depending on the severity of eating disorder symptoms (for further description of TAU, see the section ‘Explanation for the choice of comparators’). All participants will be assessed at baseline and at 12- and 24 weeks post baseline (see Fig 1). A stratified block-randomization with concealed randomization sequence will be conducted.

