## Methods: Participants, interventions, and outcomes

### Study setting

Recruitment will take place from eating-disorder outpatient facilities in the Mental Health Services in the Capital Region of Denmark and in Region of Zealand of Denmark, as well as private hospitals, residential treatment sites, private practice psychologists, and interest groups. The randomized clinical trial will be conducted at the University Hospital at Mental Health Center Copenhagen, Capital Region of Denmark. The SPIRIT 2013 reporting guidelines has been applied together with the SPIRIT 2025 explanation and elaboration: updated guideline for protocols of randomized trials [28,29]. A completed SPIRIT checklist has been provided as an additional file (see S2 File: SPIRIT checklist).

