### Sample size

Our primary hypothesis posits a difference in treatment effect between the two groups, as measured by the Eating Disorder Examination Questionnaire (EDE-Q). Previous research has established a reliable clinically significant change of 0.83 on the EDE-Q [59], with a standard deviation (SD) of 1.31 [60]. We define the minimal clinically important difference as a true difference of 0.83 between the experimental and control group means. Calculating effect sizes reveals that to detect treatment difference using a t-test, with 80% power and a significance level of 0.05, a sample size of 40 subjects per group is required Attrition rates in RCT’s investigating psychological treatment for eating disorders has been reported to range from 0 to 34.2% for studies with immediate follow-up and 2.4% to 21.4% for studies with three-month post intervention follow-up [61]. To account for potential attrition and deviations from the assumptions, we have increased the total sample size by 20% to 96 participants.

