### Assignment of interventions: Allocation

#### Sequence generation.

Patients giving written consent are randomly allocated to either VR-based avatar intervention or standard treatment. Randomization is performed by a centralized, concealed computer-generated randomization system in REDCap (see “Data management section”). Randomization will be stratified by recruitment site to ensure both groups have a comparable range of TAU interventions.

Block size is created by an independent statistician and will be unknown to the trial assessors, trial therapists and clinicians overseeing TAU. The randomized intervention allocation is concealed to assessors and to the statisticians performing the analysis until the analysis of the resulting data has been finalized.

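### Randomisation is stratified by recruitment site, but the stated ANCOVA names only treatment and baseline value; if site is prognostic, the primary test is mildly conservative

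*Protocol article*

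**What the plan says.** Under *Sequence generation*, the protocol article gives both the stratifier and its purpose: "Randomization will be stratified by recruitment site to ensure both groups have a comparable range of TAU interventions". Allocation is "in a 1:1 ratio (48 participants in each group"). Besides public outpatient units in two regions, *Study setting* lists recruitment sources "as well as private hospitals, residential treatment sites, private practice psychologists, and interest groups". Neither the number of strata nor their sizes are given.

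Under *Statistical methods for primary and secondary outcomes*, the model is "The analysis method will be ANCOVA of change from baseline with treatment as factor and baseline value as covariate". No site or stratum term is named. The same section adds: "Details of model specifications, imputation methods & assumptions, sensitivity analyses and subgroup analyses will be provided in the statistical analysis plan (SAP"), with the SAP to be public before data lock.

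Under *Sample size*, the trial is sized on an unadjusted comparison: "We define the minimal clinically important difference as a true difference of 0.83 between the experimental and control group means", "with a standard deviation (SD) of 1.31", and "to detect treatment difference using a t-test, with 80% power and a significance level of 0.05, a sample size of 40 subjects per group".

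**The concern.** Site was made a stratifier because it stands for the type of background care. *Explanation for the choice of comparators* describes very different forms of care: open-ended individual therapy, 20-week group therapy, about ten private-hospital sessions, and residential stays with meal support. A site effect on the 12-week outcome is therefore plausible, although the article does not say that it expects one.

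Stratified blocks force near-balance of sites between arms, so between-site differences largely cancel from the treatment estimate. A model without site still counts those differences as residual noise. Its standard error then overstates the true sampling error, and the test rejects too rarely. What is at stake is precision that the design has already secured. A borderline result could be missed. A positive result is not threatened.

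**Working it through.** **1. The plan's own figure.** Inputs from *Sample size*: difference 0.83, SD 1.31, alpha 0.05 (two-sided assumed), power 80%.

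n per arm = 2 × (1.960 + 0.842)² × 1.31² / 0.83² = 2 × 7.85 × 1.716 / 0.689 ≈ 39.1, rounded up to 40. The exact noncentral t gives 79.9% at 40 per arm and needs 41 for 80%, so the figure reproduces within rounding. Then 80 × 1.2 = 96. This calculation takes no credit for baseline or site adjustment.

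**2. Large-sample approximation.** Let ρ be the share of residual variance lying between sites (not documented). With perfect balance within sites, the true variance of the estimate is proportional to 1 − ρ, while the model without site uses the full variance. So:

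- ratio of model SE to true SE = 1/√(1 − ρ): 1.054 at ρ = 0.10 and 1.118 at ρ = 0.20
- actual type I error = 2 × [1 − Φ(1.96/√(1 − ρ))]: 3.9% at ρ = 0.10 and 2.8% at ρ = 0.20

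Few sites and incomplete blocks weaken this, so it was also simulated.

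**3. Simulation at the planned difference.** From the protocol: difference 0.83, SD 1.31, 80 completers. Assumed: blocks of 4, ρ from 0 to 0.20, 5, 10 or 20 equal sites or 8 unequal ones, and no correlation between baseline and outcome (matching the unadjusted sample-size basis). There were 3,000 replicates per setting. Site was either omitted or entered as fixed effects.

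| Sites | ρ | Model SE / true SD, site omitted | Type I error, site omitted | Power, omitted → fixed site term |
|---|---|---|---|---|
| 5 | 0 | 0.2926/0.3035 = 0.96 | 4.7% | 79.1 → 78.4% |
| 5 | 0.05 | 0.2930/0.2868 = 1.02 | 4.9% | 80.3 → 81.5% |
| 5 | 0.10 | 0.2905/0.2779 = 1.05 | 3.6% | 81.1 → 83.0% |
| 5 | 0.20 | 0.2874/0.2690 = 1.07 | 3.4% | 82.3 → 86.0% |
| 10 | 0 | 0.2945/0.3015 = 0.98 | 4.7% | 79.1 → 78.5% |
| 10 | 0.05 | 0.2934/0.2860 = 1.03 | 4.4% | 80.0 → 80.9% |
| 10 | 0.10 | 0.2931/0.2827 = 1.04 | 4.4% | 80.3 → 82.3% |
| 10 | 0.20 | 0.2909/0.2657 = 1.09 | 4.0% | 82.4 → 87.4% |
| 20 | 0 | 0.2941/0.2982 = 0.99 | 5.6% | 79.1 → 75.7% |
| 20 | 0.05 | 0.2944/0.2951 = 1.00 | 4.0% | 79.0 → 78.7% |
| 20 | 0.10 | 0.2936/0.2854 = 1.03 | 4.1% | 80.7 → 79.4% |
| 20 | 0.20 | 0.2924/0.2742 = 1.07 | 3.5% | 80.0 → 83.5% |
| 8 unequal | 0 | 0.2938/0.2959 = 0.99 | 4.8% | 79.6 → 78.7% |
| 8 unequal | 0.05 | 0.2932/0.2909 = 1.01 | 4.8% | 79.7 → 79.9% |
| 8 unequal | 0.10 | 0.2907/0.2769 = 1.05 | 3.9% | 80.8 → 82.4% |
| 8 unequal | 0.20 | 0.2880/0.2712 = 1.06 | 3.7% | 82.7 → 86.7% |

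Simulation error is about √(0.05 × 0.95/3000) = 0.4 points on a type I error near 5%, so small differences between rows should not be read closely.

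**4. A separate simulation.** This used 96 randomised, six unequal strata, blocks of 4, one sixth missing and baseline correlation 0.5 (strata, block size and correlation are assumptions). At ρ = 0.10 the SE ratio was 0.2555/0.243 = 1.05, with type I error 3.8%. At ρ = 0.20 the SE was about 10% too wide, with type I error 3.5%. The direction and rough size agree with step 3.

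**The case against.** The strongest reply is that the article leaves model details to a SAP that is not shown. Nothing in the model sentence says that other terms are excluded, and a site term may already be planned. That limits the weight of the point, and a reader should not infer that the trial has decided against adjusting for site. The deferral does not remove the point, because the article does more than name ANCOVA: it lists the factor and the covariate. A SAP that follows that list omits the stratifier, and one that adds site should say so openly as an addition to the published model.

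Four stronger readings are tempting, and the documents do not support them.

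- **That the standard errors are certainly too wide.** This needs site to predict outcome beyond baseline. No between-site variance is given, and with ρ = 0 there is no widening.
- **That the trial falls short of its planned power.** The sample size rests on an unadjusted t-test, and the model without site keeps at least 79% in every setting above. A larger loss, 74% down to 66% at ρ = 0.20, appears only if the true difference is taken as 0.60, a value found nowhere in the protocol.
- **That the imputation model will omit site.** Imputation methods are expressly left to the SAP.
- **That adding site always helps.** With 20 sites as fixed effects, power falls by 3.4 points at ρ = 0 and by 1.3 points at ρ = 0.10. The list of recruitment sources makes many small strata possible.

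**Conclusion.** The point holds in conditional form. The article stratifies by site and states a model without it. If site explains 10% of residual variance, the standard error is about 3% to 5% too wide; at 20% it is about 6% to 10% too wide. Type I error is about 3.4% to 4.4% over these settings, and 3.4% to 3.8% in the runs with five or six strata. With 5 or 10 sites, the power forgone at the 0.83 difference is about 2 points at 10% and 4 to 5 points at 20%. At 5% or less, the change from adding fixed site terms runs from about −3 to +1 points.

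The number of strata, the site variance and the block size are assumptions, and step 3 covers complete cases only. The error is on the conservative side, so this is a modest loss of available precision and not a threat to validity.

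**What to change.** Before data lock, state the primary and secondary ANCOVA with treatment, baseline value and the randomisation stratum. Pool small sites by a pre-specified rule applied blind to allocation, for example by TAU sector (public outpatient, private hospital, residential, primary or private sector), or enter site as a random effect. Carry the same term into the imputation model and into the mixed models for the exploratory outcomes. If site is to be left out, give the reason.

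The cost is wording and a few degrees of freedom out of roughly 80 to 96 participants. The risk is a loss of up to about 3 points of power if many tiny sites are entered as fixed effects and site turns out not to be prognostic, which is why pooling or a random effect is advised. Pooling has its own small price: a sector is coarser than the stratum used at randomisation, so differences between sites within a sector stay in the residual and a little conservatism may remain.

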#### Interim analyses.

N/A no interim analyses will be performed in this trial.

#### Methods for additional analyses (e.g., subgroup analyses).

Details of subgroup analyses will be provided in the SAP, that will be made publicly available prior to data lock (i.e., before the dataset is finalized and analysis starts).

#### Methods in analysis to handle protocol non-adherence and any statistical methods to handle missing data.

For the primary and secondary endpoints, missing data will be multiply imputed under missing at random (MAR). Sensitivity analyses will involve exploring departures from the MAR assumption, i.e., a tipping point analysis is planned to assess how far must the imputed values deviate from the MAR assumption before the conclusion of the primary analysis is overturned

For the exploratory endpoints, missing data will be implicitly handled by the linear mixed effects model.

#### Plans to give access to the full protocol, participant level-data and statistical code.

We will deliver a completely deidentified data set to an appropriate data archive for sharing purposes no later than 5 years after finishing the last 24 weeks follow up interviews.

### Oversight and monitoring

#### Composition of the coordinating center and trial steering committee.

The trial will be supervised by a project management group (PMG). The PMG will consist of the primary investigator of the study (PI), the research collaborators on one of the inclusion sites in the Mental Health Services in the Capital Region, the daily leader of the trial, and the principal therapist of the trial. The PMG will have monthly meetings during the recruitment period.

#### Composition of the data monitoring committee, its role and reporting structure.

A Data Monitoring Committee (DMC) will not be set up. Adverse events will be monitored according to ethical standards and continuously reported to the Danish Health Research Ethics Committee, overseeing the trial. The Danish Health Research Ethics Committee have the authority to recommend pausing or terminating the trial.

#### Adverse event reporting and harms.

The main known side-effect to VR-based interventions is cyber sickness, resembling common motion sickness. If encountered, it typically resolves after a few VR-sessions as tolerance develops. VR-based psychotherapy is generally well tolerated [64]. Hence, we do not expect any serious adverse events to occur. As this is an emotion focused intervention set in an immersive condition, we do expect that participants may experience distress as a temporary part of the therapeutic process, especially in the first sessions. Participants will be informed of this enabling them to make informed decisions regarding participation and adherence, and to prepare them for managing any potential transitory reactions [65]. As detailed in the section ‘Intervention description’, the therapists will monitor the participants’ levels of distress throughout the therapy course, adjusting the intervention accordingly. If a participant becomes overwhelmed, therapists will assist with in-session and at-home calming strategies and follow up the next day by phone or text. Participants will also continue receiving standard care before, during, and after the intervention to support safety.

Any acute events impacting emotional or physical health will initiate immediate action, including contacting the participant’s primary clinician, notifying relatives, or escorting the participant to acute psychiatric care, as appropriate. The following serious adverse advents are monitored throughout the study: 1) hospital admissions; 2) suicide attempts; 3) violent incidents necessitating police involvement (whether victim or accused); 4) self-harm; 5) deaths.

#### Frequency and plans for auditing trial conduct.

The PI of this study is a member of the PMG thus making sure information concerning trial conduct reaches members in the research group. Information regarding the trial is shared monthly.

#### Plans for communicating important protocol amendments to relevant parties (e.g., trial participants, ethical committees).

All protocol amendments need to be approved by the Committee on Health Research Ethics of the Capital Region of Denmark. Deviations from the published protocol will be documented in the trial registration on ClinicalTrials.gov (Identifier: NCT06345040).

#### Plans for, patient or public involvement in the design, conduct, and reporting of the trial.

The VR-based avatar intervention of this study was initially co-developed with individuals with a diagnosis of eating disorder (n = 8) and clinicians with expertise in eating disorder treatment (n = 5), whose input shaped the VR content and therapeutic manual to ensure relevance and acceptability. Additionally, participants in the feasibility study (n = 10) delivered feedback on the intervention, further informing the treatment protocol. Feedback on the experience of completing the assessment battery was also provided by an individual with lived experience. The analysis and dissemination phases will also include participants in the trial, ensuring their perspectives in the interpretation and communication of the findings.

#### Dissemination plans.

All results positive, negative, or non-significant will be published. Study results will be disseminated to the scientific audience, the public and trial participants, who in their written consent, have declared a wish to be informed. Discussions regarding the study and its results will be shared in scientific publications, conference presentations, clinical interest groups but also importantly in relevant patient interest groups.

#### The use of AI.

Generative AI (OpenAI’s ChatGPT) was used as a writing support tool during the preparation of the protocol. The tool was used primarily to support reference searching during protocol development and for language editing and restructuring of text to improve clarity. All substantive ideas, research design, hypotheses, and technical and clinical details were developed by the research team and collaborators. All references and scientific claims have been manually verified. No text has been included without review, editing, and approval by the research team. The use of AI has been limited to support drafting and formatting, not content generation or decision-making.

#### Trial status.

Protocol version and date: 1, 02.04.24Recruitment start: 26.02.24Clinical Trials registration: 14.03.2024 (within 21 days of enrollment of the first participant, in compliance with section 801 of the Food and Drug Administration Amendments Act (FDAAA 801), to ensure transparency)Estimated recruitment end: 26.10.25Estimated completion of data collection: 26.04.26Estimated date of results: 01.11.2026

### Discussion

As stated, eating disorder interventions are recommended to include psychological therapies [7], but in many cases these yield insufficient outcomes [8–10],with dropout rates ranging from 20–70% [11,12] and relapse rates of 30% upon completion [12–14]. This highlights a need for the development of therapies aimed at targeting characteristics that may maintain eating disorder symptoms. As research suggests that a subordinate relationship with the eating disorder voice, a critical inner voice experienced by patients with an eating disorder, may play a maintaining role in eating disorder pathology, this may present a meaningful target for intervention [16,18,21–22]. AVATAR therapy for psychosis has proven effective in reducing the power of a psychotic voice, hereby alleviating the voice hearer’s distress [23,25]. A pilot study has provided preliminary evidence on the feasibility and acceptability of applying this computerized intervention to address the power dynamic between patients with an eating disorder and their inner eating disorder voice [17]. This trial explores the efficacy of this intervention for eating disorders, using avatars in virtual reality.

#### Embodied externalization and dialogue as an important mechanism of change.

Prominent interventions for eating disorders such as Cognitive-Behavioral Therapy, the Maudsley Model of Anorexia Nervosa Treatment for Adults, and Focal Psychodynamic Therapy, typically focus on challenging the ‘irrationality’ and ‘unhelpfulness’ of thought content [21]. However, these traditional approaches often overlook the patient’s relationship with these thoughts [21]. In contrast, avatar-based therapy, incorporates therapeutic modalities such as relational and narrative therapies, which emphasize addressing the subordinate stance that patients often adopt towards these problematic thoughts or parts of the self. As evident within the frame-work of avatar-based therapy, relational approaches often utilize externalization techniques to enable patients to challenge the influence of these thoughts or parts of self by facilitating a dialogue with them [21,27].

The application of avatars or computer-generated representations expands upon techniques like the chair work method, a dialogue-based approach that externalizes a part of the self in a physical form and space [21,27]. The chair work technique involves using two chairs to represent different aspects of the self, with participants physically shifting between chairs to adopt the perspectives of each part in real time [22,18,27]. These more embodied approaches, has been shown to be particularly useful for patients, who like those with eating disorders, often over-identify with a specific part of the self, enhancing their ability to differentiate themselves from their inner experiences [21,27].

However, the chair work method still depends heavily on the participants’ imagination to embody the different parts of the self. In contrast, employing avatars allows patients to engage in a dialogue with a part of self, as if it were an *external independent entity*. Findings in cognitive science, suggest that experiencing oneself acting on an external entity, rather than on an internal representation, enhances the feeling of agency (e.g., the ability to make independent choices and act on them) [66]. Building on this, avatars not only help patients differentiate themselves from their inner experiences but also promote a sense of autonomy, potentially offering a more effective means to create dissonance between the self and the eating disorder, and achieve greater sense of control.

Compared to traditional talking therapies avatar-based interventions also poses new possibilities and challenges in the therapeutic relationship. When the therapist voices the eating disorder’s often abusive content, it requires considerable training in the method to ensure the dialogue remains therapeutically contained and it poses new ethical concerns (also see discussion on ‘Ethical implications’) [67]. On the other hand, patients with an eating disorder often show ambivalence towards recovery, rendering motivational work a central part of treatment. Avatar-based intervention may help mitigate a common difficulty in this treatment phase: the tendency for therapists to argue for change, unintentionally positioning patients to defend the eating disorder [68,69]. By externalizing the eating disorder through an avatar, the patient can respond to the disorder directly, from other parts of the self, replacing the oppositional dynamic between therapist and patient with internal dialogue.

